# ***Eligibility criteria***

# The inclusion and exclusion criteria are summarized in Table 1. The main entry criterion is known type 2 diabetes plus >2 other MS traits, as defined according to the IDF criteria [16], i.e. waist circumference M >94 cm F >80 cm; triglycerides >150 mg/dl and/or HDL cholesterol M <40 mg/dl F <50 mg/dl or specific treatment; and BP >130/85 mmHg or specific treatment. Additional requirements are age from 45 to 75 years, duration of diabetes > 1 year, BMI 27-40 kg/m2, sedentary lifestyle for at least six months, ability to walk without assistance and eligibility after cardiovascular evaluation. Patients having any condition that limits or contraindicates the exercise will be excluded from the study.

# ***Recruitment, randomization and baseline evaluation***

# Patients fulfilling the above criteria will be recruited in 22 outpatients clinics nationwide (see Appendix 1 and Figure 1) and subsequently randomized to two arms:

# mixed (aerobic+ resistance) exercise, prescribed and supervised + exercise counseling (EXE);

# conventional treatment, including exercise counseling (CON);

# for 12 months.

# All patients attending the outpatients clinics participating in this study will be evaluated for eligibility. The recruitment process will include 3 visits designated as R1, R2 and R3 (Table 2)

# During the first visit (R1), eligible patients will be registered in the IDES database, together with their demographic, anthropometric and clinical data, and will be asked to participate in the study; those who accept will be invited to read and sign a statement of informed consent (see Appendix 2), whereas those who do not accept will be excluded from the study. Each patient will undergo two specialist consultations: a visit of an ophthalmologist for funduscopic evaluation and a cardiologic examination for resting ECG and an ECG treadmill test for cardiovascular disease (CVD) evaluation when needed.

# On the second visit (R2), after excluding from the study those patients who will be eventually found to have severe retinopathy or CVD on the ophthalmologic and cardiologic visits, all subjects will be asked to fill in two forms, the ITALIAN SF-36 health survey (ISF-36) [17] and the WHO – Diabetes Treatment Satisfaction Questionnaire (WHO-DTSQ) [18] for baseline assessment of subjective health status perception and diabetes treatment satisfaction. A structured individualized counseling intervention [19] will be then administered to all patients, independent of the group assignment, and blood and urine samples will be collected and sent via express courier to the central laboratory for being assayed for group A biochemical measurements at baseline (Table 3). The Minnesota Leisure Time Physical Activity (LTPA) questionnaire [20] will be also given to all patients for retrospective assessment of the volume of physical activity at baseline. Finally, patients will be informed about group assignment, as established by the use of a centralized permuted-block randomization computer program and subsequently assessed at the Metabolic Fitness Center for basal evaluation of physical fitness.

# On the third visit (R3), basal anthropometric and blood pressure (BP) measurements will be obtained and registered in the database, together with results of laboratory tests performed centrally. Subsequently all patients will receive a treatment regimen aimed at achieving optimal glycemic, lipid, BP and body weight targets, as established by current guidelines. This program will eventually include glucose-, lipid- and BP-lowering agents as needed and, when indicated, anti-platelet drugs. For ethical reasons, drugs will be also adjusted throughout the study to attain target levels and to account for reduced needs. The treatment regimen will include also a dietary prescription, which will be preceded by a preliminary nutritional evaluation with assessment of BMI and the individual patient requirements and preferences. The diet will contain 55% calories from complex carbohydrates, 30% from fat, and 15% from protein. Since all patients are overweight or obese, they will receive a low calorie diet (negative balance of 500 kcal/day, not <1500 Kcal in males and 1200 Kcal in females), calculated by adding the estimated energy expenditure from non-conditioning or non-volunteer and conditioning or volunteer physical activity to basal metabolism estimated using the gas exchange analyzer FitMate (Cosmed, Rome, Italy). Baseline LTPA will be calculated by multiplying the weekly hours spent in the various activities, as reported in the Minnesota LTPA questionnaire, by the metabolic equivalent (MET) score of each activity, and expressed as METs· h–1 · week–1. Patients will be also given a diary to be filled in daily with type of physical activity performed and time spent in each of them (Figure 2 and Table 4). Finally, patients will receive a list of intermediate, group B biochemical measurements, to be performed at each center laboratory immediately before the next visit (Table 3), will be prescribed.

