**Exclusion criteria**

1. All patients with a history of central nervous dysfunction such as hemiparesis, myelopathies, cerebral ataxia, significant musculoskeletal deformities such as an amputation, dysmetria, or scoliosis, patients with movement abnormalities or arthritis limited by pain when exercising.
2. A history of clinical evidence of severe cardiovascular disease which may limit or be a contraindication for exercise.
3. Clinical evidence of vestibular dysfunction
4. Angina and related symptoms
5. Postural hypotension defined as a fall in arterial blood pressure when changing position of >20 mmHg (systole) or >10 mmHg (diastole)
6. History of plantar sores.

**Table 2:** Recruitment and follow-up process

| **Phase** | **Visit** | **Action** |
| --- | --- | --- |
| **Recruitment** | **R1** | Registration of eligible patients in the IDES database together with their demographic, anthropometric and clinical data  Participation acceptance and informed consent sign  Prescription of ophthalmologist and cardiologist consultation for retinopathy and CVD evaluation |
| **R2** | Return of ophthalmologist and cardiologist evaluation  Administration of the SF-36 and the WHO-DTSQ questionnaires  Administration of the Minnesota LTPA questionnaire  Structured individualized counseling intervention  Collection of blood and urine samples for baseline, Group A biochemical measurements and forwarding to the central laboratory via express courier  Appointment at the Metabolic Fitness Center for metabolic fitness assessment and strength evaluation  Communication of the group assignment  Information about the exercise program (EXE group) |
| **R3** | Registration of results of baseline, group A biochemical measurements  Registration of data from Minnesota LTPA questionnaire  Nutritional evaluation and prescription of a treatment regimen according to the current guidelines, including diet prescription  Consignment of a diary for prospective assessment of physical activity  Prescription for intermediate, group B biochemical measurements |
| **Follow-up** | **F1** | Intermediate anthropometric and blood pressure measurements  Registration of results of intermediate, group B biochemical measurements (with eventual treatment regimen modification)  Registration of data from the diary of physical activity  Structured individualized counseling reinforcement  Prescription for intermediate, group B biochemical measurements |

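### Baseline weight, waist and blood pressure are taken at R3, after patients learn their group at R2; they should be recorded before disclosure, and Table 2 should show them

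*Protocol*

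**What the plan says.** Three parts of the Protocol bear on this point.

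- **Order of events in the text** (Recruitment, randomization and baseline evaluation). At R1, eligible patients are "registered in the IDES database, together with their demographic, anthropometric and clinical data". At R2 they complete the questionnaires and receive counseling, and "blood and urine samples will be collected and sent via express courier to the central laboratory". The R2 account then closes: "Finally, patients will be informed about group assignment". The baseline fitness evaluation follows. The text for the next visit begins: "On the third visit (R3), basal anthropometric and blood pressure (BP) measurements will be obtained and registered in the database". The treatment regimen is prescribed after that, still at R3.
- **Table 2.** The R1 row has "Registration of eligible patients in the IDES database together with their demographic, anthropometric and clinical data". The R2 row has "Communication of the group assignment", together with information about the exercise program for the EXE group. The R3 row covers laboratory results, the activity questionnaire, nutritional evaluation and prescription, the diary and the next laboratory request. It has no entry for body measurements or BP, whereas the rows for F1 to F4 list both.
- **Use of these values.** Secondary outcomes include between-group differences in the reduction of BP, BMI and waist, and responder thresholds for BMI (reduction above 1) and waist (reduction above 5 cm). The Statistical analysis plan section compares changes from baseline with an unpaired t-test or Mann-Whitney test, and adjusts the target analyses for baseline status.

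**The concern.** A baseline used in a change score should not depend on the arm. Here, patients know their arm when weight, waist and BP are first recorded as baseline values, and those in EXE have been told about the exercise program. Two routes to an arm-related shift are open:

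- **Behaviour.** Patients may alter activity or eating between R2 and R3 according to what they were told. The interval is not stated, but it must at least allow couriered samples to be assayed centrally and the results returned.
- **Measurement.** BP and waist depend on the observer and on the patient's state, and the Protocol describes no masked assessor. Weight is much less exposed to this route.

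An error of this kind enters the treatment comparison directly and does not shrink with sample size. Separately, Table 2 does not show where these baselines are taken. A site working from the table alone would find body measurements before treatment only at R1 and no baseline BP entry at all.

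**Working it through.** **Step 1. Order of baseline collection against disclosure.**

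| Variable | Where the text takes the baseline | Relative to disclosure |
|---|---|---|
| HbA1c, lipids (central laboratory) | R2, described before disclosure | Before |
| SF-36, treatment satisfaction | R2, described before disclosure | Before |
| Weight/BMI, waist, BP | R3 | After |
| Fitness | Fitness Center, after disclosure at R2 | After |

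Table 2 agrees that disclosure is at R2. Its R2 row lists the fitness appointment ahead of the communication of assignment, but making an appointment is not carrying out the test.

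**Step 2. Which late baselines feed a between-group change endpoint.** BMI, waist and BP do. Fitness does not: the secondary outcomes list it only through its relationship with risk factors. The point therefore concerns weight/BMI, waist and BP.

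**Step 3. How a shift propagates.** Let the EXE baseline be shifted by δ relative to CON because the arm is known, with the final values unaffected.

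- Unadjusted change: the difference in mean change moves by −δ, the whole of the shift.
- Regression on baseline with slope b: the adjusted difference moves by −bδ. With b between 0 and 1 the bias is reduced but not removed.

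The sign of δ is unknown, so the treatment effect could be overstated or understated.

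**Step 4. The plan's own sample size.** From Sample size calculation: difference 0.5, SD 1.6, power 90%, α = 0.05 (two-sided assumed).

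n = 2 × (1.960 + 1.282)² × 1.6² / 0.5² ≈ 215.2 per arm, or 216 rounded up, against 215 stated. This reproduces. The point does not rest on this figure, which only fixes the n for Step 5.

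**Step 5. Illustration of sensitivity.** The Protocol gives no SD of change for BP, waist or BMI and no estimate of δ, so δ is expressed in SDs of the change score and its values are assumptions. With no true effect, the two-sided 5% test rejects with probability Φ(z − 1.96) + Φ(−z − 1.96), where z = δ / √(2/n).

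| Assumed δ (SD of change) | z at 215 per arm | Rejection, 215 per arm | Rejection, 300 per arm |
|---|---|---|---|
| 0 | 0 | 5% | 5% |
| 0.05 | 0.52 | 8% | 9% |
| 0.10 | 1.04 | 18% | 23% |
| 0.20 | 2.07 | 55% | 69% |

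For scale, if the SD of change were 15 mmHg for systolic BP and 5 to 6 cm for waist (both assumed), 0.10 SD would be 1.5 mmHg and 0.5 to 0.6 cm. The table shows what a given shift would do. It is not evidence that a shift occurs.

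**The case against.** The strongest case for leaving the plan alone has several parts, and much of it stands.

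- **The primary endpoint is untouched.** HbA1c is sampled at R2 before the described disclosure and assayed centrally. The affected outcomes are secondary, and the Protocol introduces them as exploratory. This stands and sets the severity.
- **The R3 readings precede the treatment regimen.** This also stands: the risk is measurement or behaviour bias, not a baseline taken on treatment.
- **Regression adjustment is foreseen.** The Statistical analysis plan section allows for it where arms differ. It would reduce a shift but not remove it, and the first-named comparison is unadjusted.
- **No size or direction can be shown.** This stands. The rejection rates only restate the assumed shift.

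A reader might also infer more than the Protocol supports:

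- *That allocation concealment failed.* Randomization is central and computer-generated. The issue is measurement after disclosure.
- *That staff are known to be unmasked.* The text says only that patients are informed. Staff knowledge is a reasonable inference, but it is not stated.
- *That Table 2 contradicts the text.* It confirms disclosure at R2, and its R1 entry matches the text. Its R3 row is incomplete: waist and BP are missing, while BMI is implied by the nutritional evaluation, which the text says includes it.
- *That two rival baselines are defined.* Only the R3 values are labelled basal; R1 is the eligibility visit.
- *That patients lost between R2 and R3 have no baseline data.* Body measurements exist from R1. At most this applies to BP, which is not named there.
- *That the 10-year risk outcome is biased too.* The Protocol does not list the inputs of the risk tables.

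**Conclusion.** The point holds in a limited form. As written, baseline weight/BMI, waist and BP are measured after patients know their arm, these variables are compared as changes from baseline, and no masked assessment is described. An arm-related shift would pass one-for-one into the unadjusted comparison. Its size and sign cannot be derived from the Protocol; the range of 8% to 55% at 215 per arm rests wholly on assumed shifts of 0.05 to 0.20 SD. The missing entries in Table 2's R3 row are an omission that should be repaired at the same time.

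The HbA1c comparison is unaffected, and so are the lipid and questionnaire baselines, which are also described before disclosure. This is a modest correction to secondary endpoints, worth making because it is nearly free. It does not have to be resolved before the trial can be relied on for its primary question.

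**What to change.** 1. At R2, measure and record weight, waist and BP, and release the assignment only once that record is complete.
2. State that these R2 values are the baseline for every change and responder endpoint on these variables, and for the baseline status used in the target analyses.
3. Amend the R2 and R3 text, and add the measurements to the R2 row of Table 2.

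**Cost.** The patient is already in clinic at R2, so this is a re-ordering within an existing visit plus a text and table edit. The baseline is taken slightly earlier, ahead of the R3 regimen; the blood sample for HbA1c and lipids is already timed that way.

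**Two changes not recommended.** Substituting R1 values for some patients would mix baseline definitions, and R1 does not name BP. Moving the fitness test ahead of disclosure is not simple re-ordering, because the Cardio-respiratory fitness section requires two run-in sessions first, and fitness is not a listed between-group change endpoint.

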***Follow-up and final evaluation***

During treatment period, the patients recruited will be seen at 3-month intervals for three intermediate visits and one final visit at the end of the 12-month period (Table 2).

At visits F1, F2 and F3, intermediate anthropometric and BP measurements will be obtained and registered in the database, together with the volume of physical activity performed in the previous 3 months and results of laboratory tests performed locally. Where needed, the treatment regimen will be modified according to current guidelines and changes in therapy will be registered in the database. All patients will be also given a new counseling intervention aimed at verifying, encouraging and reinforcing their compliance to diet and physical exercise, either supervised (EXE group) or non-supervised (CON group), and, except for visit F3, a prescription for intermediate, group B biochemical measurements, to be performed at the individual center laboratory immediately before the next visit (Table 3). At visit F4, final anthropometric and BP measurements will be obtained and registered in the database, together with the volume of physical activity performed during the last 3-month period. Blood and urine samples will be also collected and sent via express courier to the central laboratory for group A biochemical measurements at the end of the study (Table 3), and results will be subsequently registered in the database. Assessment of health status perception and diabetes treatment satisfaction via the ISF-36 and the WHO-DTSQ will be repeated and data will be entered in the database. Finally, patients will be given an appointment at the Metabolic Fitness Center connected to the outpatient clinics for physical fitness assessment at the end of the study.

# **Treatments**

***Exercise program***

The training program for the EXE group consists of twice a week supervised sessions of 75 min duration of mixed (aerobic and resistance) exercise, for 12 months.

Aerobic training will be performed using treadmill, step, elliptical, arm or cycle-ergometer. Transformation of maximal oxygen consumption (VO2max)in exercise load will be performed by the use of a software (Wellness System, Technogym SPA, Gambettola, Italy) or a dedicated spreadsheet, which allow calculation of the individual training load for each equipment from VO2max using the American College of Sports Medicine (ACSM) equations [21].

Resistance training will consist of 4 resistance exercises, i.e. thrust movement on the transverse plane (chest press or equivalent), traction movement on the frontal plane (lateral pull down or equivalent), squat movement (leg press or equivalent), trunk flexion for the abdominals, and three stretching positions. Intensity will be adjusted according to improvements in predicted VO2max and 1RM, as recorded throughout the study, thus resulting in further increments of working loads. In addition, caloric expenditure will be increased progressively by 0.1 kcal/kg body weight/session every month (Table 5).

Subjects in the EXE group will be allocated to either moderate-intensity aerobic (at 55% of predicted VO2max) and resistance (at 60% of predicted 1 Repetition Maximum, RM) or high-intensity aerobic (at 70 % of predicted VO2max) and resistance (at 80% of predicted 1RM) exercise, depending on the centres, which have been preliminary assigned to exercise patients at moderate- or high-intensity. Exercise and duration of aerobic training and number of series will be managed to obtain the same caloric expenditure per kg body weight, independent of the intensity level of exercise.

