***Secondary outcomes***

Secondary research goals include an exploration of :

- Percentage of patients in each group that after 12 month achieve one or more of the following targets: HbA1c <6.5% or HbA1c reduction >0.5%; total cholesterol <175 mg/dl; LDL cholesterol <100 mg/dl; HDL cholesterol >40 mg/dl; triglycerides <150 mg/dl; systolic blood pressure (BP) <130 mmHg; diastolic BP <80 mmHg; BMI reduction >1; waist circumference reduction >5 cm.
- Difference between groups in terms of reduction of HbA1c, serum triglyceride and LDL-cholesterol, systolic and diastolic BP, BMI and waist circumference and increment of serum HDL-cholesterol.
- Difference between groups in terms of reduction of number and/or dosage of glucose-, lipid- and BP-lowering drugs.
- Difference between groups in terms of reduction of global cardiovascular 10-year risk (UKPDS risk engine tables).
- Difference between groups in terms of improvement of well-being.
- Difference between groups in terms of direct medical costs and direct and indirect social costs.
- Dose/response relationship between the quality (volume and intensity) of exercise training and modifiable cardiovascular risk factors.
- Relationship between physical fitness at baseline and during the study and modifiable cardiovascular risk factors.

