***Statistical analysis plan***

The c2 test for categorical variables and the Student’s t test or the corresponding nonparametric Mann-Whitney test for continuous variables will be utilized to compare patients’ characteristics at baseline. The efficacy of intervention on primary and secondary endpoints will be assessed using the unpaired t-test or the Mann Whitney U test for continuous variables, by comparing between-groups changes from baseline to end-of-study. For categorical variables (i.e. medications), logistic regression analysis will be applied, with end-of-study rate of use included in the model as the dependent variable and baseline rate of use and study arm included as covariates.

To account for change in medication throughout the 12-month period, multiple regression analysis will be performed, with baseline-to-end-of-study changes as dependent variable and treatment at baseline and treatment initiation during the study as dichotomous variables (yes versus no), whereas drug dosage will not be taken into consideration.

Within group end-of-study vs. baseline values will be compared using the McNemar test for categorical variables and the Wilcoxon signed ranks test for continuous variables. To identify independent predictors of HbA1c changes from baseline, a multiple regression analysis was applied, with mean value of METs, baseline HbA1c values, gender, age, and changes in HOMA-IR, BMI, waist, total, LDL-cholesterol and HDL-cholesterol, and hs-CRP as covariates forced in the model.

Multivariate analysis techniques (multiple or logistic regression) will be used to adjust for differences in the distribution of one or more parameters between the two arms, whereas the ANOVA trend test will be applied for evaluating the relationship of volume and intensity of exercise training (dose/response) and fitness variation with modifiable cardiovascular risk factors.

The likelihood to achieve glycaemic and nonglycaemic targets after 12 months will be estimated using logistic regression, adjusted for baseline status (on-target vs. not-on-target).

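### Exercise intensity is assigned by centre, but the exploratory dose/response analysis names an ANOVA trend test with no allowance for centre

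*Protocol*

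**What the plan says.** The protocol's Exercise program section gives two EXE regimens, moderate and high intensity. The regimen a patient receives is set "depending on the centres, which have been preliminary assigned to exercise patients at moderate- or high-intensity". Patients "will be recruited in 22 outpatients clinics nationwide" (Recruitment, randomization and baseline evaluation). The protocol does not say how centres were assigned to an intensity or how many have each level.

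Prescribed supervised volume does not differ between patients. All EXE patients have "twice a week supervised sessions of 75 min duration of mixed (aerobic and resistance) exercise, for 12 months", the work is arranged "to obtain the same caloric expenditure per kg body weight, independent of the intensity level of exercise", and one monthly progression applies to everyone (Table 5, 3.0 to 4.1 kcal/kg per session).

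Secondary outcomes, introduced as exploratory, include: "Dose/response relationship between the quality (volume and intensity) of exercise training and modifiable cardiovascular risk factors". For this goal the Statistical analysis plan section says that "the ANOVA trend test will be applied for evaluating the relationship of volume and intensity of exercise training (dose/response"), and it uses the same test for fitness variation. It names no centre term, centre-level analysis or mixed model. The adjustment described in the same sentence is for differences between the two arms, not between intensity groups. Centre appears only as a stratification factor for the EXE versus CON randomisation (Type of randomization).

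**The concern.** All EXE patients in a centre share one intensity, so intensity is a centre-level factor. Two problems follow if EXE patients are compared by intensity as though they were independent.

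- **Confounding.** Each centre has its own staff and an associated fitness centre with its own instructor (Organization). Drugs are adjusted throughout the study, guided at 3, 6 and 9 months by local laboratory results. Case mix may differ too. Any of these can move HbA1c, lipids or blood pressure, and all of them travel with intensity. A fixed centre effect in an EXE-only model does not help, because it is aliased with intensity.
- **Precision.** The independent units for intensity are 22 centres, not about 300 EXE patients. With any positive ICC the patient-level standard error is too small.

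Volume raises a different issue. Because one supervised schedule applies to every EXE patient, differences in achieved volume come from attendance and diary-recorded activity. Both arise after randomisation and are chosen by the patient.

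At stake is a claim that one intensity outperforms the other, or that more exercise produces more benefit, made with more certainty than the design can give.

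**Working it through.** **The plan's own figure.** Inputs (Sample size calculation): SD 1.6, difference 0.5, α = 0.05 (taken as two-sided), power 90%. n per arm = 2 × [1.6 × (1.960 + 1.282)/0.5]² = 215.2, against 215 stated. It reproduces. It concerns EXE versus CON only; no sample size is given for the intensity comparison.

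**Assumptions not in the protocol.** 22 equal centres, 11 at each intensity; ICC 0 to 0.10; SD 1.6 used for the outcome.

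**EXE patients per centre.** 600/2 = 300 EXE patients, and 300/22 = 13.6. After 25% dropout, 225/22 = 10.2.

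**Reading A: moderate versus high among EXE patients, centre ignored.** Design effect DE = 1 + (m − 1) × ICC. True type I error = 2 × [1 − Φ(1.96/√DE)].

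| ICC | DE, m = 13.6 | Type I | DE, m = 10.2 | Type I |
|---|---|---|---|---|
| 0 | 1.00 | 5.0% | 1.00 | 5.0% |
| 0.01 | 1.13 | 6.5% | 1.09 | 6.1% |
| 0.02 | 1.25 | 8.0% | 1.19 | 7.2% |
| 0.05 | 1.63 | 12.5% | 1.46 | 10.5% |
| 0.10 | 2.26 | 19.3% | 1.92 | 15.8% |

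A simulation of 20,000 trials with 14 EXE patients per centre gave 6.5%, 8.0%, 12.6% and 19.5% at ICC 0.01, 0.02, 0.05 and 0.10. A t-test on centre means stayed near 5%.

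**Reading B: ordered trend CON/moderate/high, scores 0/1/2, centre effect shared by both arms.** With m patients per arm per centre, the mean score is 0.75. The sum of squared centred scores is 22m(0.5625) + 11m(0.0625) + 11m(1.5625) = 30.25m. The centred scores sum to −0.5m in a moderate centre and +0.5m in a high centre. Hence DE = 1 − ICC + (22 × 0.25m²/30.25m) × ICC = 1 − ICC + 0.182 × m × ICC. At ICC 0.01, 0.05 and 0.10, type I error is 5.2%, 5.9% and 6.7% for m = 13.6, and 5.1%, 5.5% and 6.0% for m = 10.2.

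**Power for an HbA1c difference of 0.5 between intensities** (300 EXE patients, m = 13.6, 22 − 2 = 20 df).

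- Patient-level test, clustering ignored: SE = 1.6 × √(4/300) = 0.185, power 77%.
- EXE centre means: SE = 0.185 × √DE. Power is 73%, 68%, 63%, 52% and 40% at ICC 0, 0.01, 0.02, 0.05 and 0.10.
- Arm by centre-intensity interaction, no centre-by-arm variance: SE = √[4 × 1.6² × (1 − ICC)/(11m)] = 0.261 at ICC 0 and 0.255 at ICC 0.05. Power is 44% and 46%.
- The two centre-based analyses are equally precise when 2(1 − ICC) = 1 + (m − 1) × ICC, that is ICC = 1/(m + 1) = 1/14.6 ≈ 0.07.

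**The case against.** The goal is exploratory, one of eight secondary goals, and no sample size rests on it. EXE versus CON is randomised within centre. A reader might infer that the trial's main result is compromised; the documents do not support that.

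The protocol does not say that the trend test is confined to EXE patients or ignores centre. That is inferred from a plain ANOVA with no centre term. With two intensity levels a trend test is only a two-group comparison, so an ordered CON/moderate/high trend is at least as natural, and its inflation is small. This stands as a limit on size. It does not remove the problem: under Reading B an EXE effect equal at both intensities still gives a slope of (11 × 0.25 + 11 × 1.25)/30.25 = 0.55 times that effect, so the trend does not isolate intensity.

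A reader might also infer that volume is fixed by protocol, leaving only an adherer versus non-adherer contrast. That goes too far. Only prescribed supervised volume is fixed; diaries record non-supervised activity in both arms, so measured volume varies and a trend can be computed. What survives is how it should be labelled.

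Central assay of baseline and final samples and common guideline targets should lower the ICC. If centres were allocated to intensity at random, the harm is mainly the understated error rather than systematic bias.

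Finally, CON patients are not a complete internal control. Only EXE patients follow the supervised programme, so a within-centre contrast with CON does not remove instructor or equipment effects confined to EXE.

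**Conclusion.** The concern holds for the intensity part of the exploratory dose/response analysis. The protocol assigns intensity by centre and names a test that makes no allowance for it. A comparison of EXE patients by intensity is confounded with centre, and its type I error is about 6% to 19% for ICC 0.01 to 0.10. The figure is about 5% to 7% for the ordered three-group trend. These sizes rest on assumed ICCs, equal centres and an even split of intensities, none of which the protocol gives; at ICC 0 there is no inflation. Naming a test that does not fit the stated allocation is a defect in the text, not a detail left to an unseen SAP. It should be corrected before any intensity claim is made. For achieved volume the defect is one of interpretation: the relation is observational.

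**What to change.** 1. For the intensity comparison, replace the unadjusted trend test by a model with a random centre effect, or by an analysis of centre means, with inference on the number of centres (about 20 df).
2. Add the arm by centre-intensity interaction, with random centre and centre-by-arm effects, as a supporting analysis. It compares the within-centre EXE minus CON difference between moderate and high centres and removes centre effects shared by both arms. State that it leaves instructor and equipment effects confined to EXE.
3. State how centres were assigned to intensity and how many have each level. Report the intensity result as exploratory and not randomised between patients.
4. Report relations between achieved volume (attendance and diary activity) and risk factors as observational, not as effects of dose.

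No new data are needed. The cost is a wider interval for the intensity contrast. The interaction also has lower power than EXE centre means while the ICC is below about 0.07 (at 13.6 patients per arm per centre): 44% to 46% against 73% to 52% over ICC 0 to 0.05. That is why it is proposed as support rather than as the main intensity analysis.
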